| Endpoints | 1. Primary Endpoints:  Incidence and frequency of Dose-Limiting Toxicity (DLT)  2. Secondary Endpoints:  (1) Adverse drug reactions;  (2) Recurrence-Free Survival (RFS);  (3) Disease Control Rate (DCR);  3. Tumor Response Evaluation (per RECIST 1.1 criteria):   - Complete Response (CR): Disappearance of all target lesions; no new lesions. - Partial Response (PR): ≥30% decrease in the sum of diameters of target lesions. - Stable Disease (SD): Neither sufficient shrinkage to qualify for PR nor sufficient increase to qualify for PD. - Progressive Disease (PD): ≥20% increase in the sum of diameters of target lesions or appearance of new lesions. |
| Study Procedures | 1. Arm A: TURBT unresectable  If the recurrent tumor can't be excised by TURBT, participants will be assigned to this arm. Participants in this arm will complete the neoadjuvant therapy with Irinotecan liposome (intravenous injection, once every two weeks for 1 month, dose increasing regimen: 37.6 mg/m^2^ and 56.5mg/m^2^) and Epirubicin (intravesical instillation, once a week for 1 month, 50 mg), and the therapeutic effect was evaluated by pelvic enhanced MRI and cystoscopy. Judged by two senior urologists, patients with complete response and partial response were treated with TURBT and intravesical therapy. Patients with stable disease or progressive disease received subsequent therapy at the investigator's discretion. Participants will visit the clinic once every 2 weeks for checkups and tests.  2. Arm B: TURBT resectable  If the recurrent tumor can be excised by TURBT, participants will be assigned to this arm (Arm B). Participants in this arm will complete TURBT with immediate intravesical instillation of Epirubicin (50 mg) within 24 hours after surgery. During the induction phase (the first 1 month after surgery), participants will receive the combined therapy with irinotecan liposome (intravenous injection, once every two weeks for 1 month, dose increasing regimen: 37.6 mg/m^2^ and 56.5mg/m^2^) and Epirubicin (intravesical instillation, once a week for 1 month, 50 mg). In the next 6 months, participants will continue the intravesical instillation treatment with Epirubicin (once a month, 50 mg). Participants will visit the clinic once every 2 weeks for checkups and tests in the first month, and once every 3 months after the first month. |

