## 3.2 Secondary Endpoints

(1) Adverse drug reactions: Any noxious, unintended response to the investigational drug(s) (Irinotecan liposome + Epirubicin) at any dose, causally related to treatment (per WHO-UMC causality assessment criteria).

(2) Recurrence-Free Survival (RFS): Time from treatment initiation to histologically confirmed tumor recurrence, radiologic progression or death from any cause.

(3) Disease Control Rate (DCR): Proportion of patients achieving complete response (CR), partial response (PR) and stable disease (SD).

Note: Tumor Response Evaluation (per RECIST 1.1 criteria):

- CR: Disappearance of all target lesions; no new lesions.
- PR: ≥30% decrease in the sum of diameters of target lesions.
- SD: Neither sufficient shrinkage to qualify for PR nor sufficient increase to qualify for progressive disease (PD).
- PD: ≥20% increase in the sum of diameters of target lesions or appearance of new lesions.

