## 4.1 Overall design

Enrolled patients with anthracycline-resistant recurrent NMIBC will first undergo enhanced pelvic-abdominal MRI and cystoscopy to collect imaging and pathological data. Two senior urologists will determine whether the tumor is resectable via TURBT. If unresectable (Arm A), patients will receive neoadjuvant irinotecan liposome combined with Epirubicin per the dose-escalation protocol. Post-treatment efficacy will be assessed by contrast-enhanced pelvic-abdominal MRI. For patients with CR and PR, TURBT with intravesical therapy was performed following confirmation by two independent senior urologists. For patients with SD or PD, subsequent therapies were determined by the investigator’s discretion. If resectable (Arm B), TURBT will be performed followed by immediate intravesical Epirubicin (50 mg) instillation within 24 hours postoperatively. During the induction phase (weeks 1-4 post-TURBT), the treatment with irinotecan liposome combined with Epirubicin will be completed according to the dose - escalation regimen. During the maintenance phase (months 1-6 post-TURBT), intravesical maintenance instillation of Epirubicin will be conducted once a month for a total of 6 cycles. The safety and adverse reactions will be followed up from the induction phase, and the tumor recurrence will be assessed by pelvic and abdominal enhanced MRI and cystoscopy after combination treatment.

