## 4.4 Treatment Period Follow-up

Arm A: routine blood test, liver and kidney function, coagulation function and adverse reactions were followed up every cycle after the first cycle of Irinotecan liposomal treatment. Pelvic and abdominal enhanced MRI and cystoscopy were performed after the second cycle of irinotecan liposomal treatment. The patients who achieved CR and PR were treated with TURBT combined with intravesical therapy after judged by two senior urologists. Patients with SD or PD received subsequent therapy at the investigator's discretion.

Arm B: Routine blood test, liver and kidney function, coagulation function and adverse reactions were followed up every cycle after the first cycle of Irinotecan liposomal treatment. Pelvic and abdominal enhanced MRI and cystoscopy were performed after combination treatment.

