# 6. Eligibility Criteria

## 6.1 Inclusion Criteria

Subjects can participate in the study only if all the following criteria are met:

(1) Patients with cTa-cT1N0M0 non-muscle invasive bladder cancer (NMIBC);

(2) Disease recurrence following intravesical anthracycline-based chemotherapy;

(3) Recurrent tumors confirmed as cTa-cT1N0M0 bladder urothelial carcinoma;

(4) No prior systemic chemotherapy exposure;

(5) Measurable lesions per Response Evaluation Criteria in Solid Tumors (RECIST);

(6) Eastern Cooperative Oncology Group (ECOG) performance status 0-1.

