## 12.5 Survival Follow-up

RFS follow-up was conducted every 2 months from the last dose of medication to collect RFS information and post-study treatment information (including subsequent antineoplastic therapy and efficacy) until death or loss of follow-up or discontinuation of the study.

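### RFS in Arm A has no event for tumour that never clears, so stable disease can score as well as or better than a response

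*Protocol*

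**What the plan says.** Protocol 3.2 gives one RFS rule for the whole study: "Time from treatment initiation to histologically confirmed tumor recurrence, radiologic progression or death from any cause". The same section defines SD as the category between PR and PD, and PD as growth of at least 20% or new lesions.

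Arm A is defined by tumour that stays in place (Synopsis, Study Procedures): "If the recurrent tumor can't be excised by TURBT, participants will be assigned to this arm". Section 6.1 also requires measurable lesions at entry.

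After the second irinotecan liposome cycle, 4.4 schedules MRI and cystoscopy and divides Arm A by response. For responders: "The patients who achieved CR and PR were treated with TURBT combined with intravesical therapy after judged by two senior urologists". For the rest, 4.1 states: "For patients with SD or PD, subsequent therapies were determined by the investigator’s discretion".

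Section 12.5 continues RFS follow-up every 2 months from the last dose and also collects "post-study treatment information (including subsequent antineoplastic therapy and efficacy) until death or loss of follow-up or discontinuation of the study". Section 15.5.3 analyses RFS by Kaplan-Meier, with a log-rank test between the two groups. Arm B is resected before the combination treatment starts (4.1).

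**The concern.** Recurrence-free survival presupposes a tumour-free state. Arm B reaches one through TURBT; Arm A does not have one at time zero, and only its responders are sent to study TURBT. Under the 3.2 event list, a participant whose tumour shrinks enough to be resected becomes able to recur. A participant whose tumour stays in the bladder at stable size cannot recur and has not progressed.

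This is a fault in the value derived for each participant, so it remains even if no between-arm test is run and RFS is only described by a curve. It matters because RFS is one of two named secondary efficacy endpoints. The other, DCR, also counts SD as success. Antitumour efficacy is a stated anticipated outcome (2.2). With 6 to 9 participants per arm (section 5), each Arm A participant carries 1/9 = 11 to 1/6 = 17 percentage points of any Arm A proportion.

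**Working it through.** The protocol gives no RFS rate, event count or power, so there is no figure to reproduce. The check applies the 3.2 rule to each Arm A response category, then uses an illustration with assumed rates.

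**Step 1: the rule applied as written**

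| Post-cycle-2 status | Next step (4.1, 4.4) | RFS event under 3.2 |
|---|---|---|
| CR or PR | TURBT and intravesical therapy | At recurrence, progression or death |
| SD | Investigator-chosen therapy | None while tumour persists; only at later radiologic progression or death |
| PD on imaging | Investigator-chosen therapy | At that assessment, about month 1 |

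Persistent tumour cannot be read as recurrence. On that reading every Arm A participant would have the event at time zero.

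Two hypothetical records show the result. Record 1: PR, TURBT at 1.5 months, histologically confirmed recurrence at month 6, so RFS = 6 months. Record 2: SD at month 1, tumour still present, no 20% growth by month 10, so no event and RFS above 10 months. Record 2 was never tumour-free and scores better.

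**Step 2: 6-month RFS in Arm A**

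Assumptions, none from the protocol: PD in 10%, with the event at month 1; responders (proportion r) have TURBT at 1.5 months and 50% recurrence over the next 12 months; SD participants (proportion 0.9 − r) have 20%, 50% or 80% radiologic progression over the 12 months after the month-1 assessment; constant hazards.

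As written: S(6) = r·exp(−h_r × 4.5) + (0.9 − r)·exp(−h_p × 5).

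- h_r = −ln(0.5)/12 = 0.0578, so exp(−0.260) = 0.771
- h_p at 20%: −ln(0.8)/12 = 0.0186, so exp(−0.093) = 0.911
- h_p at 50%: 0.0578, so exp(−0.289) = 0.749
- h_p at 80%: −ln(0.2)/12 = 0.1341, so exp(−0.671) = 0.511

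Example, r = 0.7 and 50% SD progression: 0.7 × 0.771 + 0.2 × 0.749 = 0.540 + 0.150 = 0.69. With r = 0: 0.9 × 0.749 = 0.67.

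| Responders | As written, SD progression 20% | As written, 50% | As written, 80% | Event-free time, SD and PD as events: r × 0.771 |
|---|---|---|---|---|
| 0% | 82% | 67% | 46% | 0% |
| 30% | 78% | 68% | 54% | 23% |
| 50% | 75% | 69% | 59% | 39% |
| 70% | 72% | 69% | 64% | 54% |

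As response rises, the as-written figure falls slightly in the first case, is flat in the second and rises in the third. The last column is a different endpoint, not the true value of the stated one.

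**Step 3: direction of the effect**

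Mean RFS restricted to 12 months, with assessment at month 1 and constant hazard afterwards (risks are those reached by month 12):

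- Responders with 40% recurrence: 9.6 months
- SD with 0%, 20%, 40%, 60% or 80% progression: 12.0, 10.9, 9.6, 8.2 or 6.5 months
- PD: 1.0 month

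SD outscores response only when its progression risk is below the responders' recurrence risk. With 20% SD progression, non-responders average 10.9 months if all have SD, but 0.5 × 10.86 + 0.5 × 1.0 = 5.9 months if half have PD, against 9.6 for responders.

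**The case against.** A reader might infer that non-response in general lengthens RFS, or that the Arm A curve is biased upward most strongly when the regimen fails. The documents do not support either. Radiologic progression is a named event, so PD shortens RFS. SD participants can still progress or die, and the protocol gives no rates to show which group fails sooner. The contrast of 82% with 0% at no responders depends on holding PD at 10%; with PD at 50% and 20% SD progression the as-written figure is 0.5 × 0.911 = 46%. It also compares two different endpoints.

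Three further points can be made for the plan. Adding progression and death gives participants with tumour in place a route to an event, as in a progression-type composite. Lack of response can be seen separately in the CR/PR/SD/PD categories. Following participants through later therapy is a recognised strategy, and censoring rules may sit in an SAP that is not shown.

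The last point stands: how therapy given after clearance is handled is not part of this finding. The first two soften the consequence without removing it. The route to an event is open only if SD later turns into progression or death, and separate response categories do not change what the RFS curve counts. The time origin and the event list are fixed in the protocol, so an SAP could not make persistent tumour an event without changing the stated endpoint.

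**Conclusion.** The point holds for stable disease. Applied exactly, 3.2 counts an Arm A participant with SD who was never tumour-free as recurrence-free until radiologic progression or death, and no other section corrects this. Such a participant can score as well as or better than a responder who was resected and then recurred. This follows from the text alone.

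The size rests on assumptions. With 10% PD and both SD progression and responder recurrence at 50% over 12 months, the 6-month figure is 67% to 69% whether no one or 70% of participants respond, so the curve says almost nothing about response. At other rates it moves either way, and no direction of bias can be claimed.

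The consequence is limited to the Arm A and pooled RFS curves and the comparison with Arm B, where the same label describes a different state. RFS is secondary, no decision rule uses it, and the primary DLT endpoint is unaffected. The definition should be changed, but it does not threaten the study's main result.

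**What to change.** In 3.2, the synopsis and 15.5.3:

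- Keep the term RFS for resected participants: Arm B from TURBT, and Arm A responders from their TURBT. Describe the Arm A subset only, because it is selected on response after baseline.
- For all Arm A participants, report an event-free time from treatment initiation. SD or PD at the post-cycle-2 assessment, where the participant does not proceed to study TURBT, is an event at that assessment date. Later recurrence, progression or death is also an event.
- Do not pool these two differently defined times, and do not compare them by log-rank test.

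Under this rule record 1 above has an event-free time of 6 months and record 2 of 1 month.

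Residual tumour after TURBT should not be added as an Arm A event, because 4.4 schedules MRI and cystoscopy after cycle 2 and lists no post-TURBT clearance assessment for that arm.

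The cost is wording. Response and TURBT are already recorded in the course of the study, and treatment does not change. The downside is a less favourable Arm A figure and a smaller RFS set.

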## 1.2 Therapeutic Challenges in NMIBC

The standard care for NMIBC involves Transurethral resection (TURBT) followed by adjuvant intravesical therapy. Among chemotherapeutic options, anthracycline-based chemotherapeutic agents, particularly Epirubicin, have emerged as a first-line intravesical chemotherapy drugs for bladder cancer due to their potent antitumor activity and favorable safety profile. These agents are also widely used in treating other malignancies such as breast cancer and gastric cancer [3]. The mechanism is to inhibit topoisomerase II activity, thereby blocking DNA replication and transcription to suppress tumor cell proliferation. In addition, Epirubicin can intercalate between DNA base pairs, inducing DNA double-strand breaks and promoting tumor cell apoptosis [4]. Although bladder cancer cells demonstrate initial sensitivity to first-line chemotherapeutic agents like Epirubicin, the majority of patients develop varying degrees of acquired resistance within several years, resulting in elevated postoperative recurrence rates, increased tumor aggressiveness upon recurrence and the greater technical difficulty in surgical resection of recurrent lesions. Therefore, addressing this acquired chemoresistance represents a critical therapeutic challenge in NMIBC management.

Tumor heterogeneity represents one of the greatest challenges in contemporary cancer therapeutics. Emerging evidence from multiple studies has demonstrated that epigenetic alterations in tumors serve as a pivotal mechanism underlying therapy resistance and poor clinical outcomes in cancer patients [5-7]. Under drug selection pressure, tumor cells adapt to their microenvironment through a fundamental remodeling process spanning multiple molecular levels---including DNA, RNA, and protein networks. For instance, tumor subclones harboring specific driver mutations may acquire selective advantages over neighboring cells, ultimately driving clonal evolution and conferring therapeutic resistance. Multiple post-hoc analyses of tissue specimens from prior bladder cancer chemotherapy trials have demonstrated that mutations in DNA damage repair (DDR) pathway genes and other molecular markers exhibit predictive value for treatment efficacy in muscle-invasive bladder cancer (MIBC) [8-10].

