## 4.2 Dose Escalation Regimen

The dose-escalation scheme is designed based on a comprehensive evaluation of non-clinical in vitro pharmacodynamic data, existing clinical efficacy evidence and Safety profiles.

Arm A: Participants in this arm will complete the neoadjuvant therapy with irinotecan liposome (intravenous injection, once every two weeks for 1 month, dose increasing regimen: 37.6 mg/m2 and 56.5mg/m2) and epirubicin (intravesical instillation, once a week for 1 month, 50 mg).

Arm B: In the induction phase, the first three participants received a reduced dose of irinotecan liposomes (37.6 mg/m2, once every two weeks) in combination with standard intravesical EPI chemotherapy (50 mg, once a week) during the first cycle. If the combination was well tolerated, the irinotecan liposome dose was escalated to the full dose (56.5 mg/m2, once every two weeks) in the second cycle. The remaining three participants received the full dose of irinotecan liposomes (56.5 mg/m2, once every two weeks) along with standard EPI (50 mg, once a week) in both treatment cycles. Epirubicin was given at a fixed dose of 50 mg q1w for 4 cycles. In the maintenance phase, Epirubicin 50 mg q1m was intravesical instillation for a total of six cycles.

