### 15.5.2 Analysis Variables

Primary Endpoint: DLT

Secondary Endpoint: Adverse drug reactions, RFS, DCR,

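### In Arm A the only endpoint derived from tumour response, DCR, groups stable disease with response, whereas the protocol's TURBT rule groups it with progression; DCR therefore cannot show shrinkage or conversion to TURBT

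*Protocol*

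**What the plan says.** Objective 1 (Protocol 2.1) includes the efficacy of the neoadjuvant combination. Section 3.2 lists three secondary endpoints: adverse drug reactions, RFS and DCR. DCR is the "Proportion of patients achieving complete response (CR), partial response (PR) and stable disease (SD"). Section 15.5.2 repeats the list: "Secondary Endpoint: Adverse drug reactions, RFS, DCR".

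The categories follow RECIST 1.1. Section 3.2 has "SD: Neither sufficient shrinkage to qualify for PR nor sufficient increase to qualify for progressive disease (PD") and "PD: ≥20% increase in the sum of diameters of target lesions or appearance of new lesions". No minimum duration of SD is given.

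For Arm A, section 4.2 fixes the course: "Participants in this arm will complete the neoadjuvant therapy with irinotecan liposome (intravenous injection, once every two weeks for 1 month". Section 4.4 times the assessment: "Pelvic and abdominal enhanced MRI and cystoscopy were performed after the second cycle of irinotecan liposomal treatment". Sections 4.1 and 4.4 and the synopsis send CR and PR on to TURBT with intravesical therapy after two senior urologists have judged the case. For the rest, the synopsis says "Patients with stable disease or progressive disease received subsequent therapy", at the investigator's discretion.

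Section 15.5.3 plans DCR with a 95% CI and a CMH or chi-square comparison between groups. It gives no reference rate.

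**The concern.** A patient is in Arm A because the recurrent tumour cannot be removed by TURBT. Two results would answer the neoadjuvant question: how many tumours responded, and how many patients then went on to TURBT. Neither is listed as an endpoint in 3.2 or 15.5.2.

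DCR places SD on the same side as CR and PR, whereas the protocol's next-step rule places SD on the same side as PD. The two therefore divide the same patients differently. A DCR figure alone does not tell a reader whether its numerator is made up of responders or of unchanged tumours. With SD accepted at a single early assessment, a high DCR is compatible with no shrinkage at all, and the efficacy part of Objective 1 would rest on RFS and on a figure that cannot separate these cases.

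**Working it through.** **Stated figure.** The protocol gives no DCR target, reference rate or power. Its only relevant number is enrolment (section 5): 6 to 9 per arm, so 2 × 6 = 12 and 2 × 9 = 18, as stated.

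**Timing.** Two cycles at two-week intervals make up a one-month course (4.2), and imaging follows cycle 2 (4.4). That puts the assessment at about day 28. Section 4.3 allows a delay of up to 2 weeks after a DLT, hence about day 42 at the later end.

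**The two groupings in Arm A.**

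| Category | DCR (3.2) | Next step (synopsis, 4.1, 4.4) |
|---|---|---|
| CR, PR | counted | TURBT with intravesical therapy |
| SD | counted | investigator's discretion, grouped with PD |
| PD | not counted | investigator's discretion |

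**An arm with only SD.** DCR = 6/6 = 100%, Clopper-Pearson 95% CI 54.1 to 100%; with nine patients, 9/9 = 100% (66.4 to 100%). The CR+PR rate in the same patients is 0/6 (0 to 45.9%) or 0/9 (0 to 33.6%). No patient would be on the protocol's CR/PR path to TURBT.

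**Growth needed for PD by size.** Assume exponential growth and volume proportional to diameter cubed. A 20% diameter increase is 1.2³ = 1.728-fold in volume, and log2(1.728) = 0.789 doublings. The volume doubling time must be no longer than 28 / 0.789 = 35.5 days, or 42 / 0.789 = 53.2 days for imaging at day 42. Doubling times of 60, 90 and 180 days add 11.4%, 7.5% and 3.7% to the diameter in 28 days, all SD. This covers only the size limb of PD; a new lesion is PD at any growth rate.

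**DCR of a regimen with no responses.** Let q be the probability of PD by the assessment, from growth or new lesions. Then expected DCR = p = 1 − q, and P(at least 5 of 6) = 6p⁵(1 − p) + p⁶. The values of q are assumptions; the documents give none.

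| q | Expected DCR | P(at least 5 of 6) | P(at least 7 of 9) |
|---|---|---|---|
| 5% | 95% | 0.967 | 0.992 |
| 10% | 90% | 0.886 | 0.947 |
| 20% | 80% | 0.655 | 0.738 |
| 30% | 70% | 0.420 | 0.463 |

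**Arm B.** Under 4.1, Arm B tumours are resected before the combination starts. After a complete resection no target lesion remains in which RECIST response could be measured, so the between-arm DCR test in 15.5.3 does not compare like with like.

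**The case against.** The strongest reply is that this is a phase I trial of 12 to 18 patients with DLT as the primary endpoint. DCR is secondary, has no success threshold, and stands beside RFS. Nothing in the protocol says that a high DCR will be presented as proof of activity. Response has to be classified in every Arm A patient to apply the TURBT rule, and an SAP may tabulate the categories. The synopsis also numbers tumour response evaluation as item 3 of its endpoints row, so it would be too strong to say that response is absent from the endpoints. But that item gives only definitions. No rate is derived from it, and 3.2 and 15.5.2 agree on a list with DCR alone. The choice of endpoints is fixed in the protocol and is not a detail left open for an SAP. RFS is a time-to-event measure and does not show how many tumours shrank or became resectable.

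Three stronger readings are tempting and should not be drawn:

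- That SD at week 4 is simply the natural course of the disease, so that an inactive regimen is bound to score high. Section 1.2 says that "the majority of patients develop varying degrees of acquired resistance within several years", but this concerns how long resistance takes to appear, not the growth of an existing recurrence. The 5-year recurrence range in 1.1 does not give a growth rate either, and both sections describe recurrence as aggressive.
- That the protocol declares SD a failure. It does not use that word. The discontinuation criteria (6.3) name progression only, discretion does not exclude TURBT, and responders too have finished the one-month combination by then.
- That week 4 is stated, or is the only imaging. It is derived, and 12.2 and 12.3 also list tumour imaging. However, neither section ties a repeat or confirmatory assessment to DCR.

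**Conclusion.** The point holds as a mismatch between endpoint and decision rule in Arm A. It follows from the text alone: SD counts towards DCR without a minimum duration, SD is grouped with PD for the next step, and no listed endpoint reports response or conversion to TURBT. An arm with only SD would report 100%, and this needs no assumption about growth.

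The size of the distortion for an inactive regimen is not established. Expected DCR of 95 to 70%, with a probability of 0.97 to 0.42 of at least 5 of 6 counted as controlled, rests on assumed progression rates of 5 to 30% and on no responses. DCR would be lower if early growth were fast or new lesions frequent; it would fall to 50% only if half the patients progressed by the assessment.

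This is a low-cost improvement to a secondary endpoint. It does not affect the DLT analysis. Removing DCR altogether would be a matter of preference and is not needed.

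**What to change.** Amend sections 3.2, 15.5.2 and 15.5.3 and the synopsis together:

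- Add two Arm A secondary endpoints: the CR+PR rate at the assessment after cycle 2, and the proportion going on to TURBT under the existing two-urologist rule. Give each an exact (Clopper-Pearson) 95% CI, the method that 15.5.3 already names for the DLT rate.
- Tabulate CR, PR, SD and PD separately for Arm A.
- Keep DCR as descriptive, state the assessment at which SD is judged, and say that DCR alone does not support a claim of activity.
- Drop the between-arm DCR test in 15.5.3.

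The MRI, cystoscopy and urologists' judgement are already planned, so no new data, visits or patients are needed, and no treatment rule changes. The costs are a protocol amendment, a headline response figure that can only be equal to or lower than DCR, and wide intervals with 6 to 9 patients (for example 0/6 has an upper limit of 45.9%).

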## 1.1 Overview of Bladder Cancer

Bladder cancer has emerged as one of the most common genitourinary malignancies in China, currently ranking as the eighth most frequently diagnosed cancer among Chinese male populations. With its characteristically high incidence, frequent recurrence patterns, and substantial mortality burden, this disease represents a major public health challenge in contemporary China [1]. Among histological subtypes, non-muscle invasive bladder cancer (NMIBC) constitutes approximately 75% of incident cases at initial diagnosis, representing the predominant clinical presentation. This form demonstrates particularly aggressive recurrence patterns, with published 5-year recurrence rates ranging from 31% to 78% across various clinical series [2]. The substantial recurrence risk, coupled with potential progression to muscle-invasive disease, underscores the critical need for effective therapeutic interventions. To mitigate recurrence and disease progression, adjuvant intravesical instillation therapy following transurethral resection of bladder tumor (TURBT) has been established as the standard treatment regimen for NMIBC.

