## 14.6 Disease Progression and Death

Disease progression is defined as the worsening of a participant's condition due to the studied indication, including radiological progression as well as progression of clinical symptoms and signs. The appearance of new metastatic lesions from the primary tumor or progression of existing metastases is considered disease progression.

In the study population of this trial, "disease progression" is an expected outcome and should not be reported as an AE term. When disease progression occurs, the events used to confirm progression should be reported as AEs. For example, if a participant experiences seizures determined to be related to brain metastases, the AE term should be recorded as "seizures" rather than "disease progression" or "brain metastases."

Similarly, events leading to the diagnosis of disease progression—even if they meet criteria such as being life-threatening, requiring hospitalization or prolonging hospitalization, or causing permanent or severe disability/functional impairment (significant limitation in the ability to perform normal life functions)—should not be reported as SAEs. However, if it is uncertain whether the AE is due to disease progression, it should be reported as an SAE.

During the safety follow-up period, deaths assessed by the investigator as potentially caused by symptoms or signs of disease progression must be reported as SAEs.

The term "death" should not be used as an SAE term but rather as an outcome. The adverse event that caused or led to death should be recorded as the SAE term. If the cause of death cannot be determined at the time of reporting, the SAE term should be recorded as "death of unknown cause."

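### In Arm A, a persistent lesion that becomes muscle-invasive without 20% growth is scored as PR or SD and counted as disease control; whether it is an RFS event is unclear

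*Protocol*

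**What the plan says.** Section 3.2 sets the response categories by measurement. Partial response is "PR: ≥30% decrease in the sum of diameters of target lesions", progression is "PD: ≥20% increase in the sum of diameters of target lesions or appearance of new lesions", and stable disease is whatever falls between the two. The synopsis repeats the rule: "Progressive Disease (PD): ≥20% increase in the sum of diameters of target lesions or appearance of new lesions". No category carries a condition on T stage, depth of invasion or histology. DCR is the proportion with CR, PR or SD.

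RFS in section 3.2 is "Time from treatment initiation to histologically confirmed tumor recurrence, radiologic progression or death from any cause". Radiologic progression is not defined there or elsewhere. Section 13.1 refers tumour assessment back to RECIST v1.1.

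The population is defined by stage. Section 6.1 requires "Recurrent tumors confirmed as cTa-cT1N0M0 bladder urothelial carcinoma", and section 1.1 describes the recurrence risk as "coupled with potential progression to muscle-invasive disease".

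In Arm A (tumour judged not resectable by TURBT) the lesion is left in place through about a month of study treatment. MRI and cystoscopy follow the second irinotecan liposome cycle (section 4.4). TURBT is then planned only for participants with CR or PR (sections 4.1 and 4.4).

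Section 14.6 describes disease progression for safety reporting as a worsening due to the studied indication, "including radiological progression as well as progression of clinical symptoms and signs".

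**The concern.** Participants are selected because their disease has not reached muscle, and the background names progression into muscle as one of the two risks that justify treatment. Yet the efficacy rules have no place for that event when it occurs in a lesion already being measured. The planned MRI, cystoscopy and TURBT specimen could each bring it to light, but the scoring rule gives the finding no effect.

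At stake is the meaning of DCR in Arm A. A participant who has left the disease state that defined eligibility would be reported as controlled, and this misclassification can only favour the treatment. For RFS, two assessors could reasonably classify the same participant differently.

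**Working it through.** **Inputs.** Response rules, DCR and RFS: section 3.2 and synopsis. Arm size: 6 to 9 (section 5). Assessments and TURBT rule: sections 4.1 and 4.4. Upstaging rate: not given in the documents.

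**The plan's own figure.** Two arms of 6 to 9 give 2 × 6 = 12 and 2 × 9 = 18, which matches the stated total of 12-18.

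**Step 1: apply the rules to an illustrative 30 mm lesion that has become T2, with no new lesions.** Change = (post − 30) / 30.

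| Post-treatment size | Change | Category | In DCR? |
| --- | --- | --- | --- |
| 35 mm | 5/30 = +16.7% | SD | yes |
| 30 mm | 0% | SD | yes |
| 25 mm | −5/30 = −16.7% | SD | yes |
| 20 mm | −10/30 = −33.3% | PR | yes |
| 15 mm | −15/30 = −50% | PR | yes |

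T stage does not enter the rule, so the result is the same at Ta, T1 or T2. PD first appears at 36 mm (6/30 = +20%).

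**Step 2: weight of one participant in Arm A.** The shift is 1/n: 1/9 = 11.1 points and 1/6 = 16.7 points. If all others are controlled and one participant is reclassified, with Clopper-Pearson 95% intervals (the protocol names this method for the DLT rate; its use for DCR here is illustrative):

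| n | DCR as written | DCR with one reclassified |
| --- | --- | --- |
| 6 | 100% (54.1 to 100) | 83.3% (35.9 to 99.6) |
| 9 | 100% (66.4 to 100) | 88.9% (51.8 to 99.7) |

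**Step 3: chance that it happens at all.** P(at least one) = 1 − (1 − p)^n. The values of p are assumptions chosen to show a range.

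| Assumed p | n = 6 | n = 9 |
| --- | --- | --- |
| 5% | 26.5% | 37.0% |
| 10% | 46.9% | 61.3% |
| 20% | 73.8% | 86.6% |

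**Step 4: take the same Arm A participant through the RFS events.**
- Histologically confirmed recurrence: the tumour was never removed, so this does not plainly apply.
- Radiologic progression: if read as the size rule, there is no event; if read in its ordinary sense, muscle invasion newly seen on MRI is an event. The text does not choose. Invasion found only in a TURBT specimen is not a radiologic finding.
- Death: does not apply at that point.

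The RFS classification is therefore undetermined.

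**Step 5: Arm B.** The tumour is resected first. A muscle-invasive tumour that appears later would normally be a new lesion (PD) and a histologically confirmed recurrence (RFS event), so the gap largely closes there.

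**The case against.** The strongest case on the other side has five parts.

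- **RFS.** Radiologic progression is listed as an event in its own right and is not tied to the 20% rule. A reader might infer that every upstaged participant drops out of the RFS events. The documents do not support that: invasion newly seen on MRI can be read as radiologic progression, and RFS follow-up every 2 months (section 12.5) means a missed event might only be delayed. This stands; what remains is an undefined term.
- **Scope.** A reader might infer that the gap affects both arms and every kind of stage progression. It does not. Arm B is largely covered, and new nodal or distant disease would generally be a new lesion and so already PD. This stands and limits the point to T2 or higher in a persistent Arm A lesion.
- **Section 14.6.** A reader might see its broader wording as contradicting section 3.2. It governs which events are reported as AEs or SAEs and does not claim to define DCR or RFS. There is no true contradiction. Nor does it fill the gap, since it does not mention muscle invasion.
- **Histology.** Entry stage is clinical. T2 in a later TURBT specimen may be depth missed at baseline, and protocol TURBT in Arm A follows only CR or PR, so histological upstaging would be found mainly in responders. This stands and shapes the fix.
- **Importance.** The 1/n shift is the weight of any single participant, no upstaging rate is documented, and both endpoints are secondary. All of this is true. It limits the consequence but does not make the scoring correct.

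**Conclusion.** The point holds for Arm A. As written, a persistent lesion that reaches T2 or higher without 20% growth or new lesions is PR or SD and counts in DCR; nothing elsewhere in the protocol corrects this. Its status for RFS is ambiguous rather than wrong. Each such participant moves Arm A's DCR by 11 to 17 percentage points (n = 9 to n = 6), in the treatment's favour.

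The size rests on the planned 6 to 9 participants in Arm A. How often it would happen cannot be said from the documents; the 5% to 20% range above is assumed. The primary DLT endpoint is unaffected, as is most of Arm B.

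**What to change.** 1. In section 3.2 and the synopsis, state that new evidence of T2 or higher disease on the planned post-treatment MRI and cystoscopy, compared with the baseline assessment, is PD for DCR and counts as radiologic progression for RFS, whatever the diameter change. Section 4.4 plans both examinations for all Arm A participants, so responders and non-responders are assessed alike.
2. Where T2 or higher is found only in the post-treatment TURBT specimen, report DCR and RFS with and without counting it as progression, because that specimen is planned only after CR or PR and may reflect understaging at baseline.
3. State that the endpoint definition of progression is the one in section 3.2 and that section 14.6 serves AE reporting only.
4. Section 6.3(3) ties discontinuation to RECIST progression. Any treatment consequence of the revised endpoint wording is for the sponsor to reconcile.

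Cost: endpoint wording and one CRF field for stage, using examinations already planned. Downsides: DCR departs from a size-only RECIST rule, which the report should say, and DCR and RFS may look slightly less favourable.
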